## Abstract

**Background:**

Low back pain (LBP) is a prevalent condition and a socioeconomic problem in many countries. Due to its recurrent nature, the prevention of further episodes (secondary prevention), seems logical. Furthermore, when the condition is persistent, the minimization of symptoms and prevention of deterioration (tertiary prevention), is equally important. Research has largely focused on treatment methods for symptomatic episodes, and little is known about preventive treatment strategies.

**Methods/Design:**

This study protocol describes a randomized controlled clinical trial in a multicenter setting investigating the effect and cost-effectiveness of preventive manual care (chiropractic maintenance care) in a population of patients with recurrent or persistent LBP.

Four hundred consecutive study subjects with recurrent or persistent LBP will be recruited from chiropractic clinics in Sweden. The primary outcome is the number of days with bothersome pain over 12 months. Secondary measures are self-rated health (EQ-5D), function (the Roland Morris Disability Questionnaire), psychological profile (the Multidimensional Pain Inventory), pain intensity (the Numeric Rating Scale), and work absence.

The primary utility measure of the study is quality-adjusted life years and will be calculated using the EQ-5D questionnaire. Direct medical costs as well as indirect costs will be considered.

Subjects are randomly allocated into two treatment arms: 1) Symptom-guided treatment (patient controlled), receiving care when patients feel a need. 2) Preventive treatment (clinician controlled), receiving care on a regular basis. Eligibility screening takes place in two phases: first, when assessing the primary inclusion/exclusion criteria, and then to only include fast responders, i.e., subjects who respond well to initial treatment. Data are collected at baseline and at follow-up as well as weekly, using SMS text messages.

**Discussion:**

This study investigates a manual strategy (chiropractic maintenance care) for recurrent and persistent LBP and aims to answer questions regarding the effect and cost-effectiveness of this preventive approach. Strict inclusion criteria should ensure a suitable target group and the use of frequent data collection should provide an accurate outcome measurement. The study utilizes normal clinical procedures, which should aid the transferability of the results.

**Trial registration:**

Clinical trials.gov; NCT01539863, February 22, 2012. The first patient was randomized into the study on April 13th 2012.

## Background

Low back pain (LBP) is a major public health problem in many countries with resulting consequences both for the individual and society. The total cost of LBP in Sweden was estimated at €1,840 million in 2001 [1]. Interventions that reduce the prevalence of back pain would therefore contribute to improvements on a public health level and potentially have large economic benefits.

LBP has been shown to be a recurrent and sometimes persistent phenomenon [2,3]. Logically, a recurrent and sometimes persistent condition that is highly prevalent invites the idea of prevention. However, knowledge about secondary prevention, to decrease the rate of recurrence, and tertiary prevention, to decrease the intensity or extent of persistent pain for this condition is scarce [4].

In Sweden, LBP is the condition for which most people seek care from a chiropractor [5,6]. Manual treatment, which has been shown to be effective for some patients [4], is a major treatment component. Among chiropractors, the traditionally employed long-term approach for individuals with recurrent or persistent pain is a preventive protocol described as maintenance care (MC) [7-10]. Early authors have described MC as “*…a regimen designed to provide for the patient’s continued well-being or for maintaining the optimum state of health while minimizing recurrences of the clinical status*” [11] and “*…treatment, either scheduled or elective, which occurred after optimum recorded benefit was reached, provided there was no evidence of relapse*” [12].

A 2008 systematic review concluded that chiropractic MC lacked an evidence-based definition as well as evidence-based indications, frequency, and content of treatment [13]. However, since 2009, several studies have investigated the frequency and content of this preventive strategy. As suggested by the name, the aim of the treatment is to maintain a certain treatment effect (i.e., less pain or improved function) [7], and care is normally delivered at widely spaced but regular intervals over a fairly long time [14,15].

Research during 2009 and 2010 has also concluded that there seems to be a general management concept within the chiropractic profession in the Scandinavian countries with regards to secondary and tertiary prevention [7,9,10,16]. In Sweden, 98% of chiropractors who have an academic education use some form of MC [7]. This type of care is in part proactive, i.e., the clinician will encourage the patient to perform specific exercises or a training program. Typically, one will also attempt to influence the LBP problem in other ways through discussions about life style [14]. Thus, regular visits may have a supportive psychosocial function by aiding coping strategies and providing support and guidance. Manual therapy (such as spinal manipulation or mobilization) of the musculoskeletal system is included as needed, as judged by the clinician [14,17,18].

A few studies have been published on the effect of preventive spinal manipulation on spinal pain and the results have been equivocal [5,19,20], maybe due to the fact that these were small studies that did not employ the evidence regarding indications for care in their inclusion process, nor regarding frequency and treatment content in their instructions for care. Thus, more research is needed to determine the effect and cost-effectiveness of this preventive package of care. In particular, it would be important to select study subjects in accordance with the procedures that have developed from years of professional experience and to include the treatment programs and activities that chiropractors actually use for this type of therapeutic strategy. This study makes use of the available evidence in the field.

## Methods/Design

### Study aim

The study aims to investigate the effect, cost-effectiveness, and cost-utility of preventive manual care as compared to manual care given only when there is a subject-perceived need in a population of patients with recurrent or persistent LBP. The primary outcome is the number of days with bothersome pain on which the cost-effectiveness calculations will also be performed. Thus, the null hypothesis will be that the subjects in the two treatment arms will report equal numbers of days with bothersome pain.

### Setting

Forty Swedish chiropractors will collect data on consecutive patients with recurrent or persistent LBP. The clinicians recruited for this study have participated in a previous study regarding the use of preventive care [8] and have experience of how to integrate research into clinical practice. Only clinicians who reported that they use preventive care selectively were recruited. This was thought to minimize the clinicians’ bias towards either of the treatment models. One two-hour training session, describing the project in detail, was given to the clinicians in a small group seminar format. Following the seminar, a member of the research team has been conducting weekly follow-ups by telephone with the participating clinicians to ensure that the procedures are followed according to the project outline and that the data collection is performed correctly.

### Eligibility criteria

The inclusion criteria for study subjects are: presenting with LBP as the main complaint, recurrent LBP (the individual has experienced episodes of LBP in the past), or persistent LBP (more than 30 days over the past year [21]). A minimum of three months must have passed since the last treatment by a chiropractor if previously treated. This interval was chosen as research indicates that the treatment seems to have little effect after three months [22]. This was also consistent with the research team’s clinical experience. The subjects must be of working age (18 to 65 years), have access to a mobile phone and knowledge of how to receive and send text-messages (SMS), as well as be proficient in Swedish. Subjects must rate themselves as “definitely improved” by the fourth visit [23]. The exclusion criteria for patients are: pregnancy, acute trauma, cancer, infection, cauda equina, osteoporosis, and vertebral fractures. Further, subjects with completely subsidized treatment from a third party payer, such as injury compensation [24], local county council subsidization, or workplace benefits, are excluded from the study. The majority of the chiropractic patients in Sweden do not have access to subsidized treatment.

An overview of the eligibility criteria can be found in Table 1.

**Table 1 T1:** Eligibility screening

**Inclusion criteria**		**Exclusion criteria**
Baseline 1	Age 18 to 65 years	Pregnancy
	LBP with or without leg pain for more than 30 days during the past year	Chiropractic treatment less than 3 months ago
	Previous episodes	Completely subsidized treatment from third party payer
	Access to a mobile phone	Serious pathology (i.e., acute trauma, cancer, infection, cauda equina, osteoporosis, vertebral fractures) or contraindications to manual therapy
	Ability to send and receive SMS (text messages)	
Baseline 2	Self-rated “definitely improved” by the fourth treatment	Self-rated improvement being anything but “definitely improved” by the fourth treatment
Study start	Interval between treatments is one month or more	Interval between treatments never extends to one month

*LBP*, Non-specific low back pain.

### Procedures

The study procedures are shown in the flowchart in Figure 1. To resemble the clinical decision-making process, the eligibility procedure consists of two main stages; first, to find possible candidates and second, to select only the study subjects who respond favorably to treatment. According to previous research, this is congruent with the procedure used by chiropractors when making clinical decisions regarding MC [7,10].

**Figure 1 F1:**
[figure not shown]
Study procedures.

For the initial visit, patients are instructed to arrive 15 minutes early if perceived as possible candidates for the study (i.e., presenting with LBP) when the booking is made. Upon arrival before the initial visit, the patients fill in a questionnaire, baseline 1, along with a screening form with inclusion/exclusion criteria with descriptive data. If no exclusion criteria exist, the patients are then treated as usual up until the fourth visit.

A continuous assessment regarding the response to treatment is made at each visit and recorded in the patients’ files. If the patients consider themselves “definitely improved” according to the global perceived improvement scale (single question with answer options definitely worse, probably worse, unchanged, probably better, definitely better) by the fourth visit or earlier, they are candidates for the study. During the fourth visit, or prior if “definitely improved”, the questionnaires of baseline 2 are administered.

The patients continue with treatment until the clinician considers them well enough to extend the interval between treatments to one month or longer. Clinically, the study subjects then enter the MC phase and data collection can commence, i.e., the study starts. The potential subjects are informed of the study procedure and asked to sign a letter of informed consent should they wish to participate. Subjects are then randomly allocated into one of two treatment arms; symptom guided treatment (patient controlled) or preventive/MC treatment (clinician controlled).

If patients do not improve to the point where the interval between treatments can be extended to at least one month, they are not eligible to continue in the study and are excluded. The cut-off interval of one month was decided after discussions within the research team based on their collective clinical experience. A time interval of less than one month was considered an active treatment regimen; this is also supported by a 2010 study [15].

Research suggests that the typical interval between treatments in an MC-regimen is two months [14]. However, a systematic review concluded that it was difficult to evaluate the effect of treatments more than three months apart [22]. The participating clinicians are therefore allowed to choose an interval between treatments of a minimum of one and a maximum of three months apart.

During the study period, study subjects in the two treatment arms continue treatment according to each protocol. The study period lasts 12 months. The treatments during these 12 months are offered with a reduced treatment fee of 50% for subjects in both treatment arms, but only for visits regarding LBP.

### Randomization procedure

Consecutively numbered opaque envelopes containing a letter with instructions are created off-site at the research center by a statistician and a research assistant. A 1:1 allocation ratio in randomly permuted blocks of different sizes according to a randomization schedule is used. SPSS v20 was used to generate the randomization code. The envelopes are opened consecutively in the presence of the study subjects as they become eligible for the study and give consent to participate.

### Blinding

The randomization is blinded to the study team in order not to influence the clinicians during the workshops and in personal contact during the inclusion process. The data collecting clinicians are unaware of the individual allocation of their patient until they have opened the envelope after consent is given. Due to the treatment modality, study subjects and clinicians cannot be blinded to the treatment.

### Sample size

A power analysis has estimated the number of subjects needed to detect a change in treatment effect of 30% (i.e., 30% fewer days of bothersome LBP) to be 177 in each treatment arm. The 30% cut-off point was decided to be a clinically important difference with regards to number of days of bothersome pain. Furthermore, a 20% (for acute pain) and 30% (for chronic pain) change in intensity measured on NRS-11 has been shown to be a clinically meaningful change [25,26].

In previous Swedish intervention studies among this group of chiropractors, compliance has been around 70 to 80% [27,28]. With a similar compliance rate in this study, we would need to include 400 study subjects when allowing for dropouts.

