### Analysis

#### *Data analysis of the primary outcome “number of days with bothersome LBP”*

Intention-to-treat [49] will be used to test the null hypothesis as described in the study aim. Outcome measures will not be imputed for participants not responding to follow-up questions as previous research using the SMS-Track system has yielded high response rates [33,36,37] and research has indicated it unnecessary when performing analysis on longitudinal data [50]. Patient related outcomes measured at the fourth visit, weekly during the study period, and at the end of the study at 12 months will be evaluated using general [51] or generalized linear models [52-54] with mean baseline values as covariates. Sex, age, the presence of leg pain, patient expectations, pain intensity, the use of painkillers, sickness, albescence, type of profession, and number of treatments before being included in the study will be considered as possible confounders. All available data will be used for data analysis. A dropout analysis will be performed to compare the study population with dropouts regarding descriptive data. Additional analyses of secondary outcomes will be performed in an explorative manner.

An analysis of cost-effectiveness and cost-utility will be performed with consideration to both the individual and societal perspectives [55]. The cost-effectiveness will be determined by comparing the incremental cost effectiveness ratio in regard to the primary effectiveness measure between the two study arms [55]. Both the incremental cost effectiveness ratio and the incremental cost-utility ratio will be calculated by dividing the difference in mean total costs by the difference in the outcome of interest between the two treatment arms. Direct medical costs considered in the study are treatment cost (treatment fee) as well as time loss during treatment and travel (an average time for travel is estimated and added to an average patient visit time). Indirect costs such as production loss will be estimated using the human capital approach where lost time is valued using the hourly wage [56]. Since the data collection is performed between 2011 and 2014, all costs will be adjusted for inflation using a 3 to 5% inflation rate with the baseline year of the study as a base year [55] and calculated in €.

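### The target of 400 does not follow from 177 per arm at 70–80% compliance: that rate calls for 443–506, and 400 would leave 140–160 per arm

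*Protocol article*

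**What the plan says.** The Sample size section of the protocol article takes two steps.

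- It sets the target effect as "a change in treatment effect of 30% (i.e., 30% fewer days of bothersome LBP"), which it treats as the clinically important difference, and gives the number needed as "to be 177 in each treatment arm".
- It then goes from earlier Swedish studies with this group of chiropractors to the total, as an allowance for dropouts: "compliance has been around 70 to 80% [27,28]. With a similar compliance rate in this study, we would need to include 400 study subjects".

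The abstract repeats the target: "Four hundred consecutive study subjects with recurrent or persistent LBP will be recruited". The Randomization procedure section specifies "A 1:1 allocation ratio in randomly permuted blocks of different sizes", so 400 means 200 per arm.

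**The concern.** The section prints both inputs (177 per arm, 70–80% compliance) and the result (400), and presents the result as derived from the inputs. The allowance is too small for the loss it is said to cover. Going from 354 to 400 adds 46 subjects, about 13%, whereas a loss of 20–30% needs an increase of 25–43% (1/0.80 = 1.25; 1/0.70 = 1.43).

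What is at stake is the claim that the trial is sized for a 30% reduction after dropout. If compliance turns out as the section predicts, the trial has less power for that difference than the 177 per arm was calculated to give. A reader who relies on the printed sample size would not know this when judging how informative a non-significant result is.

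**Working it through.** **Inputs, all from the protocol article**

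- Required per arm: 177, so 2 × 177 = 354 in total (Sample size).
- Compliance: 0.70 to 0.80 (Sample size).
- Planned total: 400, or 200 per arm at 1:1 (Sample size; Randomization procedure).
- Not printed: alpha, sidedness, power, SD and control mean. The 177 itself therefore cannot be checked and is taken as given.

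**Step 1. Try to reproduce 400**

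| Method | 80% compliance | 75% | 70% |
|---|---|---|---|
| 354 / compliance | 442.5 → 443 | 472 | 505.7 → 506 |
| 354 × (1 + loss), a common mistake | 424.8 → 425 | 442.5 → 443 | 460.2 → 461 |

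Rounding up within each arm changes the first row only slightly: 222, 236 and 253 per arm, or 444, 472 and 506 in total. Neither form gives 400. With the correct formula the gap is 43 to 106 subjects, too large for rounding.

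**Step 2. What loss does 400 allow?**

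354 / 400 = 0.885, so 400 covers a loss of 11.5%. That is 58% of a 20% loss (11.5/20) and 38% of a 30% loss (11.5/30).

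**Step 3. What does 400 leave at the stated compliance?**

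- 80%: 400 × 0.80 = 320, or 160 per arm; 17 short of 177 (9.6%).
- 70%: 400 × 0.70 = 280, or 140 per arm; 37 short of 177 (20.9%).

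**Step 4. Consequence for power (assumed values)**

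For a two-group comparison of means at two-sided 5%, find the standardised effect d for which 177 per arm gives a chosen power, then recompute at the smaller n:

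- d = (1.960 + z_power) × √(2/177)
- power at n = Φ(d × √(n/2) − 1.960)

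| Assumed power at 177 | d | n = 160 | n = 140 |
|---|---|---|---|
| 80% | 0.298 | 75.9% | 70.3% |
| 90% | 0.345 | 86.9% | 82.2% |

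At one-sided 5% the losses are similar: from 80% to 76.4% and 71.5%, and from 90% to 87.2% and 83.1%.

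**Step 5. Detectable difference at unchanged power**

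With the same SD and control mean, the detectable difference scales with 1/√n:

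- n = 160: 30% × √(177/160) = 31.6%
- n = 140: 30% × √(177/140) = 33.7%

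**The case against.** The strongest reply is that the article does not define compliance and that it need not equal the share of subjects who contribute to the primary outcome. The analysis section plans intention-to-treat on all available data, without imputation ("Outcome measures will not be imputed for participants not responding to follow-up questions"), and expects high response to the text messages. Non-responders get a reminder and then a telephone call. A subject who leaves halfway still supplies weekly counts. On that view, 140–160 per arm is a complete-case count and overstates the loss of information.

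This limits the practical size of the loss, but it does not rescue the derivation. The Sample size section itself uses the compliance figure to allow for dropouts, and it does not mention partial series as the reason for 400. Reading compliance as treatment adherence that dilutes the effect would need more subjects, not fewer: 177/0.80² and 177/0.70² give 277 and 362 per arm, or 554 and 724 in total.

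Three further points have some force.

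- The power figures rest on assumed values and a simple comparison of means, while the plan is for general or generalized linear models. They illustrate the size; the direction does not depend on them, because 140–160 is below 177 whatever power was planned.
- The 32–34% figure assumes a fixed SD for an outcome that is a bounded count of days, so it is approximate.
- What a null result excludes depends on its confidence interval, not on the enrolment target. The error misleads about the planned power; it does not bias the estimate or affect the type I error rate.

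**Conclusion.** The concern holds. The step from 177 per arm to 400 is wrong as written: at the stated 70–80% compliance the requirement is 443–506, and 400 suffices only at 88.5% retention or better. This conclusion uses printed figures alone.

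If compliance is read as the evaluable fraction, as the section uses it, the trial is 17–37 subjects per arm short. The cost is about 3 to 10 percentage points of power, assuming 177 per arm was set for 80% or 90% at two-sided 5%. Use of partial weekly data could make the real loss smaller, by an amount that the article does not allow one to calculate.

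**What to change.** Correct the Sample size paragraph and leave enrolment at 400. Suggested wording: *The power calculation requires 354 evaluable subjects. Randomising 400 supplies them only if at least 88.5% are evaluable. At 70–80% compliance, 140–160 per arm would remain, and at unchanged power the detectable reduction would be about 32–34%, assuming the same SD and control mean.*

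If 400 is defended because incomplete text-message series enter the analysis, state and justify the retention assumption actually relied on, in place of 70–80%.

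Either route changes wording only and leaves randomisation, outcome and analysis untouched. The price is a slightly less favourable statement of power or detectable difference. If the sponsor would rather keep both the 30% difference and the 70–80% assumption, the target itself would have to rise to 443–506, which means 43–106 more subjects.

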### Treatment arms

Each clinician is instructed to describe the two different treatment approaches as similar procedures, clinically both in use, when informing potential study subjects. The clinicians are asked to describe the aim of the study as a sincere wish to investigate if any of the two treatment modalities is more effective.

